## Method and analysis

### Study design

This study is a multicentre, parallel randomised (1:1) controlled trial evaluating two common treatments for completely displaced, overriding metaphyseal DRFs. Designed to avoid large interruptions in busy orthopaedic practices or emergency departments, the practical design will mirror clinical care. In-person assessments will be conducted at baseline, 6 weeks and 3 months to include physical exams, questionnaires and radiographic or other imaging assessments. Anterior-posterior and lateral radiographs of the wrist and forearm will be obtained, and complications will be tracked. Subsequent collection of questionnaires at 6 months, 1 year, 2 years and 3 years will leverage electronic surveys to reduce participant and clinical staff burden (figure 1). Additional radiographs will be collected for any participant returning to the clinic during the follow-up period. Participants will complete all study activities 3 years after fracture.

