### Sample size considerations

Sample size calculations were based on detecting a clinically meaningful difference in the Patient-Reported Outcomes Measurement Information System (PROMIS) Pediatric Computer Adaptive Test (CAT) V.2.0 - Physical Function - Upper Extremity (UE) of 4 points. PROMIS measures use a T-score metric with a mean of 50 and SD of 10 in a reference population.^18^ A sample size of 133 per arm, assuming a two-sided type I error rate of 0.05, will provide 90% power to detect a difference between arms of 4 points. To conservatively account for 20% lost to follow-up or missing data on the primary outcome at 12 months, we have inflated our sample size to 167 per arm, for a total target enrolment of 334.

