### Statistical analyses

Descriptive statistics will summarise demographics, medical history, baseline outcome measures and other clinical characteristics by arm. The participant disposition will be summarised using frequencies and proportions for all ITT participants. The study will follow Consolidated Standards of Reporting Trials guidelines for reporting results.

Analysis for the primary aim will use a mixed-effect model for repeated measures of the primary outcome, PROMIS Pediatric CAT – Upper Extremity, measured at baseline (reflecting preinjury status), 3 months, 6 months and 1 year. The model will include fixed effects for treatment arm, time as a categorical variable, and the treatment arm by time interaction term. Sex and age (continuous) will be included as covariates. Incorporation of a random centre effect will allow for separation of between-site and within-site variance components. For the repeated measures within a participant, we will assume an unstructured covariance matrix. If the model does not converge, then a simpler covariance structure (compound symmetry) will be used. We will report estimates for the mean and SD at 1 year for each arm. The between-arm difference in model-estimated 1 year means will be reported with corresponding 95% CI and p value. The primary analysis will be assessed using a two-sided type I error rate of 0.05, with no adjustment for testing of secondary or exploratory outcomes. Two sensitivity analyses will be conducted including a per-protocol analysis and analyses using multiple imputation for missing data, as described below. Model validity will be assessed via residual diagnostics. We will graphically assess the distribution of residuals to determine if there is gross departure from normality, and if so, transformations may be considered. The unstructured covariance matrix allows for differential variance across time points. If there is evidence of a differential variance between treatment arms, then the covariance matrix may be estimated separately for each arm.

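### Two fallback rules in the primary model, compound symmetry on non-convergence and optional transformation, would weaken the 1-year result if triggered, and both are cheap to replace

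*Protocol article*

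**What the plan says.** All the rules at issue are in the Protocol article, Statistical analyses. The primary analysis is a mixed model for repeated measures of the PROMIS Upper Extremity score at baseline, 3 months, 6 months and 1 year, with an unstructured within-participant covariance. The reported result is the difference between arms in model-estimated means at 1 year, with a 95% CI and p value.

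Two departures from that model are provided for:

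- Covariance: "If the model does not converge, then a simpler covariance structure (compound symmetry) will be used". No intermediate structure and no robust standard error is named. Later the paragraph gives the merit of the first-choice matrix: "The unstructured covariance matrix allows for differential variance across time points".
- Scale: residuals are inspected graphically for "gross departure from normality, and if so, transformations may be considered". No transformation is named, and nothing says that the T-score analysis stays primary.

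The target effect is set on the T-score scale in Sample size considerations, where 133 per arm "will provide 90% power to detect a difference between arms of 4 points".

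**The concern.** The two rules act on different parts of the primary result.

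A transformation changes what is estimated. The trial is sized in T-score points and promises a difference in 1-year means. A difference on a transformed scale is neither, and it converts to no single number of points.

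Compound symmetry leaves the scale alone but fixes one variance for pre-injury, 3-month, 6-month and 1-year scores. The section values the unstructured matrix for letting variances differ by visit, and the only fallback removes that property. The primary test is a single-visit contrast, so its model-based standard error would use a variance averaged over visits that may not resemble the one at 1 year. The p value and CI could then be too optimistic or too cautious.

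The two listed sensitivity analyses (per-protocol and multiple imputation) address neither the scale nor the covariance fallback.

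**Working it through.** **Inputs from the article.** Difference 4 points, two-sided alpha 0.05, power 90%, 133 per arm, 20% loss, 167 per arm and 334 in total (Sample size considerations); 1:1 allocation (Study design). The only SD given is the reference-population value: "PROMIS measures use a T-score metric with a mean of 50 and SD of 10 in a reference population".

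**The plan's own figure.** With SD 10, n per arm = 2 × (1.960 + 1.282)² × 10² / 4² = 131.4, so 132 by the normal approximation. The noncentral t gives 89.9% power at 132 and 90.1% at 133, so 133 is reproduced. Inflation: 133 / 0.8 = 166.25, so 167 per arm and 334 in total. The stated sample size is sound and implies a planning SD of 10.

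**Compound-symmetry fallback.** With complete data and a full arm-by-visit model, the 1-year estimate is the raw difference in means.

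- True SE = SD at 1 year × √(2/n).
- Model SE under compound symmetry = √(mean of the visit variances) × √(2/n).
- Ratio r = model SE / true SE. Actual type I error = 2 × [1 − Φ(1.96 r)].

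The article gives no visit SDs, so those below are assumptions, in the order baseline, 3 months, 6 months, 1 year:

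| Assumed SDs | Averaged SD | r | Type I error |
|---|---|---|---|
| 10/10/10/10 | 10.00 | 1.00 | 5.0% |
| 5/8/9/10 | √(270/4) = 8.22 | 0.822 | 10.7% |
| 6/10/8/7 | √(249/4) = 7.89 | 1.127 | 2.7% |
| 5/7/8/10 | 7.71 | 0.771 | 13.1% |
| 5/12/9/6 | 8.46 | 1.409 | 0.6% |

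The figures also depend on whether baseline is in the response. Statistical analyses includes it; Missing data lists only 3 months, 6 months and 1 year. Without baseline, 8/9/10 gives r = √(245/3)/10 = 0.90 and type I error about 7.7%; 10/8/7 gives r = √(213/3)/7 = 1.20 and about 1.8%. The direction is the same and the error is smaller in these examples.

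**How likely the trigger is.** An unstructured matrix for four visits has 4 × 5 / 2 = 10 parameters. With about 334 children, non-convergence is unlikely. Estimating the matrix separately by arm, which the section also allows, doubles this to 20.

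**Transformation.** Take a reflected log, log(61 − score), as an illustration; the constant 61 is assumed. A gain of 4 points is then

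- from 50 to 54: ln(11/7) = 0.45;
- from 46 to 50: ln(15/11) = 0.31;
- from 42 to 46: ln(19/15) = 0.24.

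One effect on the log scale therefore corresponds to different point differences depending on where a child starts.

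On whether a transformation is needed: two-group comparisons of untransformed scores were simulated at 133 per arm, complete data, with an assumed ceiling holding 31%, 50% or 62% of scores (skewness about −1.0, −1.6 and −2.2). Type I error was 5.2%, 4.9% and 4.7%. Under these conditions even a marked ceiling does not invalidate the raw-scale test.

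**The case against.** The covariance rule is fixed in advance: unstructured first, one named structure if the fit fails. Convergence failure is not a choice made on the treatment effect, and naming a fallback beforehand is good practice. A reader might infer that the covariance will be picked after looking at arm-level results; the text does not support that for this rule. A reader might also take 11% as the trial's type I error. It is not: it needs an unlikely convergence failure and visit SDs that the article does not give, and it vanishes if the SDs are equal. All of this stands. What remains is that the fallback is a poor choice when better ones cost nothing.

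On transformation, the wording is permissive and limited to gross departures, and a fuller analysis plan may settle the details. A reader might infer that the residual check is made unblinded, or that the smaller of two p values could be reported. The article does not say who sees what at that check, and it does not allow reporting the better of two scales. Simulated worst-case picking between raw and log scales gave about 7.2%, but that does not describe this plan. The article also promises the mean and SD at 1 year by arm, so it would be too strong to say that every link to the 4-point target is lost. What stands is that the article itself leaves the scale of the primary test open.

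Finally, the large-sample argument is cleanest for complete data. With up to 20% missing and a likelihood analysis under missing at random, distributional fit and covariance structure can matter more. That weakens any claim that normality is wholly irrelevant. It also strengthens the case against an over-restrictive covariance, because a wrong structure can then bias the estimate as well as its standard error.

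**Conclusion.** The point holds as a conditional weakness of the primary analysis. If the unstructured model fails to converge, the only fallback ties the 1-year standard error to a visit-averaged variance. The error can go either way: 18% too small or 13% too large in the two main illustrations, with type I error about 11% or 2.7%, and none if SDs are equal. Those figures rest on assumed SDs, complete data and baseline in the response, and the trigger is unlikely. If a transformation is adopted, the primary test no longer concerns the promised difference in T-score means and cannot be compared with 4 points; at this sample size there is little need for it. The article does not support a claim that the covariance is chosen on unblinded data or that the trial's error rate is inflated as planned. The change is worth making before arm-level outcomes are seen. The sample size calculation is unaffected.

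**What to change.** 1. State that the untransformed T-score analysis stays primary whatever the residual plots show, and that any transformed analysis is a sensitivity analysis only.
2. Replace the compound-symmetry fallback with an ordered list of structures that keep a separate variance for each visit, for example heterogeneous Toeplitz and then heterogeneous compound symmetry.
3. Add robust (sandwich) standard errors as a further safeguard. The model has a random centre effect, so they may have to cluster on about 34 sites; in that case specify a small-sample correction.

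The cost is a few sentences of specification. Robust standard errors do not correct bias in the estimate from a wrong covariance when data are missing, so item 2 is the essential part of the covariance repair. The sample size stays at 133 per arm evaluable and 167 per arm enrolled.

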### Outcomes

The primary outcome of interest is the PROMIS Pediatric CAT – Upper Extremity measured at 1 year (table 1). The measure is a validated patient-reported outcome for function that is correlated with physiological tests of function.^18^ Secondary outcomes of interest include additional measures of perceived pain captured by the Disabilities of the Arm, Shoulder and Hand – Sports / Performing Arts Module (DASH S/PA), PROMIS Pediatric V.2.0 - Pain Interference, Wong-Baker FACES pain score, and PROMIS Pediatric V.1.0 Global Health (7+2). Cosmesis (assessed by parent rating of appearance), complications, missed work (parents) or school, parent-reported satisfaction, radiographic angulation, and occurrence/number of revisions, refractures, re-reductions and reoperations will also be assessed.

**Table 1 T1:** Outcome measures and time points of analysis

	Measure	Time-point	
Primary	PROMIS Pediatric CAT V.2.0 – Physical Function – Upper Extremity^19^	1 year	
Secondary	PROMIS Pediatric CAT V.2.0 – Physical Function – Upper Extremity	6 weeks, 3 months, 6 months	
	DASH – S/PA^20^	6 weeks, 3 months, 6 months, 1 year*	
	PROMIS Pediatric V.2.0 - Pain Interference^19^	6 weeks, 3 months*, 1 year	
	Wong-Baker FACES Pain score^21^	6 weeks, 3 months*	
	PROMIS Pediatric V.1.0 - Global Health (7+2)^22 23^ – Global Score	6 weeks, 3 months, 6 months, 1 year*	
	PROMIS Pediatric V.1.0 - Global Health (7+2)^22 23^ – Fatigue interference	6 weeks, 3 months, 6 months, 1 year	
	PROMIS Pediatric V.1.0 - Global Health (7+2)^22 23^ – Pain interference	6 weeks, 3 months, 6 months, 1 year	
	Number of revisions, refractures, reductions and reoperations	1 year*	
	Other complications	1 year	
	Missed work or school	3 months*	
	Satisfaction questionnaire^6^	3 months, 6 months*, 1 year	
	Cosmesis	6 weeks, 3 months, 6 months, 1 year*	
	Radiographic alignment	6 weeks†	

* Indicates time point of clinical interest incorporated in family of hypothesis tests with adjustment for multiplicity.

† Radiographic is only collected as part of standard of care and is only mandated at the 6-week visit.

CAT, Computer Adaptive Test; DASH – S/PA, Disabilities of the Arm, Shoulder and Hand – Sports/Performing Arts Module; PROMIS, Patient-Reported Outcomes Measurement Information System.

The statistical methods detailed here focus on analyses incorporating outcomes measured through 1 year. Exploratory objectives beyond 1 year will be detailed elsewhere.

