Secondary analyses will incorporate a similar modelling strategy for all continuous repeated measures outcomes. A generalised linear mixed-effect (GLMM) model will be fit for binary and count outcomes with appropriate distributional assumptions and link functions. Specifically, Poisson loglinear GLMM models will be fit for the number of missed school days and number of missed work days of the parent(s). Logistic GLMM models will be fit for parent satisfaction, defined as parents who reported being at least somewhat satisfied, and for occurrence of revisions, refractures, re-reductions and/or reoperations. A false discovery rate correction will be applied to account for multiplicity within the prespecified family of hypothesis tests at key clinical time points for each secondary outcome (table 1). P values for additional time points and all additional exploratory analyses will not be adjusted for multiplicity.

Planned subgroup analyses of the primary outcome may include assessment of treatment effects by age group and sex. Specifically, models will be fit with interactions between the treatment arm and each of these variables. Although we anticipate being underpowered for these specific interactions, these models will be used to assess whether there is evidence that the effect of the intervention is different depending on these prespecified subgroups.

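### Missed school and work days are assigned a Poisson model with no stated allowance for overdispersion, so two tests in the false-discovery-rate family may be too liberal

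*Protocol article*

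**What the plan says.** Under Statistical analyses, the protocol article first sets a general rule for non-continuous secondary outcomes: a generalised linear mixed "model will be fit for binary and count outcomes with appropriate distributional assumptions and link functions". It then makes the rule specific for days missed: "Poisson loglinear GLMM models will be fit for the number of missed school days and number of missed work days of the parent(s".

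Table 1 (Outcomes) lists "Missed work or school" at 3 months only and stars that time point. The footnote gives the meaning of the star: "Indicates time point of clinical interest incorporated in family of hypothesis tests with adjustment for multiplicity". The method for that family is also stated: "A false discovery rate correction will be applied to account for multiplicity within the prespecified family of hypothesis tests".

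The only random effect named in the article belongs to the primary linear model: "Incorporation of a random centre effect will allow for separation of between-site and within-site variance components". The sentence that carries the primary strategy over to secondary outcomes is limited in scope: "Secondary analyses will incorporate a similar modelling strategy for all continuous repeated measures outcomes". The random effects of the count models are therefore not listed. The residual checks and fallback options in the same section are described for the primary model; none is described for the counts.

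**The concern.** A Poisson model ties the variance to the mean. Given the covariates and the centre, families with the same expected number of missed days may differ only by Poisson noise. That is a strong restriction for absence from school or work. Children aged 4 to 10 are eligible, so some may not yet attend school. Parents' working arrangements differ. The type of immobilisation is left to the surgeon, and later procedures are not restricted by the trial. Such features tend to produce many zeros together with some long absences.

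With one count per participant there is no repeated-measures term to take up that variation, and a centre effect takes up only differences between centres. If the extra variation is present and nothing in the model represents it, the standard error is too small, the confidence interval too narrow and the p value too low. Time off school and work is a result that families would weigh when choosing between sedated reduction and simple immobilisation, so a spurious difference would be noticed. A false discovery rate procedure also presumes valid input p values.

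**Working it through.** **Inputs from the protocol article.** 133 evaluable per arm, 167 per arm after 20% loss (334 in total), 1:1 allocation, 34 hospitals, two-sided 0.05. The 0.05 level is stated for the primary outcome: "assuming a two-sided type I error rate of 0.05, will provide 90% power to detect a difference between arms of 4 points". It is taken here as the nominal level for the count tests as well.

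**Inputs assumed.** The article gives no mean, variance or dispersion for missed days. Let φ be the within-centre variance divided by the mean, and take φ = 1, 1.25, 1.5, 2, 3 and 5. The simulations also assume a mean of 2, 3 or 5 days and a between-centre SD of 0.3 on the log scale.

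**Step 1: the plan's own figure.** There is none for missed days. The sample size used as an input does reproduce. For a difference of 4 and an SD of 10, the noncentral t calculation gives power 0.9015 at 133 per arm and 0.8993 at 132; 133/(1 − 0.20) = 166.25, rounded up to 167.

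**Step 2: analytic type I error.** The Poisson standard error is 1/√φ of the true one, so the test rejects under the null with probability 2 × [1 − Φ(1.96/√φ)]. For φ = 2, 1.96/1.414 = 1.386, which gives 0.166.

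**Step 3: simulation of a Poisson mixed model with a random centre intercept only.** Null case, 34 centres, N = 266, mean 3 days, negative binomial counts, 500 runs per setting.

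| φ | Model SE / true SE | Type I error, analytic | Type I error, simulated |
|---|---|---|---|
| 1 | 1.00 | 0.050 | 0.056 |
| 1.25 | 0.89 | 0.080 | not run |
| 1.5 | 0.82 | 0.110 | 0.118 |
| 2 | 0.71 | 0.166 | 0.196 |
| 3 | 0.58 | 0.258 | 0.258 |
| 5 | 0.45 | 0.381 | 0.424 |

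The median model standard error of the log rate ratio stays near 0.073 throughout, while the empirical SD rises from 0.074 at φ = 1 to 0.180 at φ = 5. The centre effect does not pick up the extra variation.

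**Step 4: does a dispersion-robust variance repair it?** This used a centre-stratified Poisson test, N = 266 and 334, mean 2 and 5, 2000 runs per setting. The ordinary version gave 0.106 to 0.120 at φ = 1.5 and 0.257 to 0.274 at φ = 3. With a robust variance the type I error was 0.044 to 0.057 for all φ from 1 to 5. The negative binomial model was not simulated; it has the same aim.

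**Step 5: the multiplicity family.** Table 1 has 8 starred rows. Testing school and work days separately makes 9 tests. The article does not name the procedure or its level, so Benjamini-Hochberg at 0.05 with independent tests is assumed. When all nulls are true and the two count tests are inflated, the probability of at least one rejection is 0.050 (φ = 1), 0.084 (1.5), 0.134 (2), 0.242 (3) and 0.411 (5). These figures include rejections of the count tests themselves, so they do not isolate the effect on other outcomes. The route to other outcomes is the step-up rule. With 9 tests the smallest p value is compared with 0.05/9 = 0.0056. If both count tests have smaller p values and are falsely rejected, the third-ranked outcome needs only p ≤ 3 × 0.05/9 = 0.0167.

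**The case against.** The strongest reply has three parts.

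First, a reader might infer that centre is the only random effect in the count models. The article does not say so. The centre sentence describes the primary linear model, and the carry-over sentence covers continuous repeated measures only. A Poisson mixed model with a participant-level random effect would still fit the stated label and would absorb variation between families. This stands: the absence of such a term is a reasonable reading, given one time point and no other random effect named, but it is an inference.

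Second, a reader might take overdispersion as established. It is not. The article reports no data on missed days; at φ = 1 there is no inflation, and at φ = 1.25 the error is only 0.080. This also stands, so the result is conditional.

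Third, dispersion checks and variance estimators are commonly left to the analysis plan, which is not shown. This stands only in part. The point is not that detail is missing. The article moves from a general promise of suitable distributions to a named one, and that choice is the restrictive option for this kind of outcome. An unseen analysis plan may add protection, but the published text commits to Poisson without it.

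A reader might go further and ask for school days to be analysed only in children with school in session, with an offset for available days. The article shows no defect that requires this. It would change the estimand from days missed to a rate in a subset, and randomisation is expected to balance season between arms.

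**Conclusion.** The concern holds in conditional form. The article fixes Poisson for two counts measured once and states nothing that would absorb variation between families. If the within-centre variance exceeds the mean and no participant-level term is fitted, the nominal 5% tests run at about 11%, 17%, 26% and 38% for ratios of 1.5, 2, 3 and 5. The dispersion ratio is an assumption, as are the Benjamini-Hochberg procedure, its level and the independence of the tests behind the family-wide figures.

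The reach is limited to two secondary tests and, through the step-up rule, the other starred outcomes. It would be wrong to infer that the trial's main result is at risk: the primary comparison is tested separately at two-sided 0.05 and does not depend on these models. This should be fixed as a cheap improvement.

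**What to change.** State the random effects of the count models and change the analysis of missed school days and parents' missed work days in one of two ways:

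- replace Poisson with a negative binomial mixed model with log link, the same fixed effects and a random centre effect; or
- keep the Poisson log-linear mean model and prespecify dispersion-scaled or sandwich standard errors.

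Choose one before outcome data by arm are seen, so that the choice cannot depend on the result.

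The cost is one sentence and no new data. With a dispersion-scaled error, the confidence interval on the log scale widens by √φ: 1.22 times at φ = 1.5 and 1.41 times at φ = 2. That is the width that the data would support. If the counts prove to be Poisson, little is lost.
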